#### Intervention group

After randomisation, participants in the intervention group will start the 12-week walking intervention.

#### WLC group

Participants in the wait-list control (delayed intervention) group will start the intervention after their follow-up measures are completed approximately 12 weeks post-randomisation.

### Measures

All measures will be conducted at the host academic institution at baseline and at the immediate post-intervention period (Fig. 1) except for focus groups, which will take place at the mid-point and post-intervention.

**Fig. 1 Fig1:**
[figure not shown]
Chart of study visits

#### Socio-demographic characteristics and medical conditions

Participants will provide socio-demographic information including their age, gender, ethnicity, marital status, living arrangements, level of education, any children, employment status and any medical conditions.

#### Health measures

*Cognitive function* will be assessed using a Montreal Cognitive Assessment (MOCA) scale designed to test mild cognitive impairment [42]. *Physical functioning* will be assessed using the Short Physical Performance Battery (SPPB) [40]. *Height* to the nearest 0.1 cm will be measured using a stadiometer (Seca AG, Reinach, Switzerland) and recorded in metres. *Weight* will be assessed using weighing scales (Tanita UK Ltd., Middlesex, UK) to the nearest 0.1 kg. *Body mass index* (BMI, kg m^−2^) will be calculated by dividing mass (kg) by height squared (m^2^). *Resting blood pressure* (BP rest, mmHg) will be measured using a portable semi-automatic OMRON sphygmomanometer (OMRON HEM705CP sphygmomanometer; Omron Matsusaka Co Ltd., Japan). *Physical activity* will be measured using ActivPAL accelerometers (PAL Technologies Ltd. Glasgow, UK) at baseline and immediate post-intervention period over a continuous 7-day period of awake and sleeping (24 h a day) except when bathing or swimming [51].

#### Questionnaires

*Loneliness* will be assessed using the 8-item UCLA Loneliness Scale (UCLA-8) [52]. *Social support* will be assessed using the 20-item Medical Outcomes Study Social Support Survey (MOSSSS) [53]. *Social networks* will be assessed using the 6-item Lubben’s Social Network Scale (LSNS-6) [54]. *Depression and anxiety* will be assessed using the 14-item Hospital Anxiety and Depression Scale (HADS) [55]. *Self-efficacy for exercise* will be measured using the revised 9-item Self-Efficacy for Walking/Exercise Scale (SEE) using a paper-and-pencil format [56]. *Satisfaction with level of social contacts* will be measured with the question “How satisfied are you with your social contacts?” [57]. *Expected outcomes and barriers for exercise* will be administered using the Expected Outcomes and Barriers for Habitual Exercise scale [58] adapted for the older adult population. Four questions related to sport competence have been deleted from the expected outcomes sub-scale due to irrelevance for this population group [58]. The expected outcomes and barriers for exercise scale have demonstrated good internal consistency from 0.66 to 0.85 and a high test-retest reliability of 0.78 in previous research [58].

#### Qualitative assessments

To understand participants’ experiences of taking part in the PAIL feasibility trial, focus groups will be conducted at mid-point (between the weeks 4 and 5) and at the end of the 12-week intervention using semi-structured discussions in small groups (four to nine people per group) of mixed gender (Additional files 5 and 6). The research team will check if any alterations will be required based on the participants’ feedback. The 32-item checklist for reporting qualitative research will guide the researcher to ensure clarity and transparency in focus groups methodology [59]. Focus groups will be audio recorded using a digital recorder and will be transcribed verbatim. An independent trained focus group leader will act as a moderator and facilitator of the focus groups [60].

#### Feasibility outcomes

The following feasibility outcomes will be assessed in this study:Attendance will be calculated as the total number of attended sessions divided by the total number of sessions of the intervention and recorded as a percentage;Recruitment rate will be calculated as the number of individuals responding to advertisements and friends’ referrals out of a total number of formal invitations given/advertisements placed (including web-based advertisements, advertisements placed in the local cohort groups and poster and leaflet material disseminated in the community). Recruitment rate will be recorded as a percentage, e.g. 25% (48/195). It is acknowledged that advertisements may reach a large number of individuals but it is impossible to quantify this;Retention rate will be calculated as the number of participants completing the study as a proportion of those randomised;The appropriateness, practicality and acceptability of the designed intervention in the proposed settings will be assessed using focus group interviews. The focus group transcripts will be analysed using a phenomenological inductive approach [61], and these data will be used to help the research team to improve the quality of the delivered intervention by informing positive changes in the methodology and design of the intervention for the future implementation in a consequent study;The assessment rate of questionnaires will be evaluated as the total number of completed questionnaires divided by the total number of questionnaires and recorded as a percentage;The appropriateness of statistical methods of data analysis will be analysed by the research team in terms of suitability to the data;A power calculation and sample size estimation will be calculated for meaningful potential future primary outcomes (e.g. loneliness or social support) using a method based on the differences in means between the intervention and control groups, using the G-power software [62];The effect size (ES) will be calculated for loneliness, social support, social networks, anxiety and depression, self-efficacy for exercise, satisfaction with level of social contacts and the expected outcomes and barriers for exercise. Means (M) and standard deviations (SD) will be used to investigate the effect size for change in loneliness using mixed between (intervention group vs. control group) and within (over time) repeated-measures analysis of variance (ANOVAs) with post-hoc comparisons.

### Data monitoring

The data monitoring committee for this project is the supervisory research team (three academic supervisors) who are independent of the trial sponsor. They will be responsible for checking data accuracy upon assembly of the final database following completion of data collection prior to data analysis. The PhD student is responsible for monitoring and reporting spontaneous adverse events or any unintended trial effects to the supervisory team, and the PI ([name]) is responsible for reporting these to the sponsor. The trial is also subject to independent audit request by the sponsor, the University of Birmingham, by a team independent to the supervisory/research team. The sponsor contact details are given below.

[name], Head of Research Governance, University of Birmingham (e-mail: [contact]).

### Data collection

Data will be collected at the university facility at screening, baseline and post-intervention period (12 weeks after the start of the intervention) (Fig. 1). After providing baseline eligibility screening, potential participants will be offered a total of five visits for health assessments at the university facility. Participants in the intervention group will have an additional sixth visit for attending the mid-point focus group. All digital data (transcripts, digital information, health assessment databases) will be stored securely on the password-protected university computers available only to the research team. All other data (e.g. eligibility screening forms, activity data and questionnaire data) will be pseudo-anonymised with a unique ID number and stored in locked filing cabinets/on password-protected university computers accessible only to the research team. Only the researchers will have access to the data.

### Sample size

As this will be the feasibility study to inform the design of the future large-scale RCT, a total target sample of 40 older adult participants will be recruited for estimation of the critical parameters [63] with 20 in the intervention group and 20 in the wait-list control group.

### Recruitment

Participants will be recruited from local neighbourhoods (households) and communities in Birmingham via a two-step strategy. First, through widespread advertisement in local media resources (newspaper, University of Birmingham website), via posters (Additional file 7) and distribution of leaflets about the study in local community centres and shops, churches, temples and mosques, local libraries, post offices, veterinary surgeries; and through advertisements via the University of Birmingham’s 1000 Elders Group [64], and Ageing Better Consortium BVSC [65]. This is to recruit an ethnically diverse sample that is reflective of the Birmingham population. Secondly, recruitment will be facilitated during the eligibility screening where potential participants will be given a copy of the information sheet (Additional file 8) or a leaflet about the study and will be asked to invite anyone else they know and who might be interested in the project, i.e. using snowball or chain recruitment by word of mouth [66].

### Recruitment and retention rates

Recruitment will be aimed to be at a rate of 10 participants a month (to a minimum of 40 participants) for estimation of the critical parameters of the feasibility study [63]. If the number of recruited participants is less than 75% by the end of the 4-month recruitment period or if the retention rate is less than 75% at 12 weeks (end-point period), changes will be made to the recruitment strategy and the intervention will run again a few months later. No targets were set for other feasibility outcomes, e.g. questionnaire completion rates or attendance at the intervention sessions.

### Progression criteria

As suggested by El-Kotob et al. [67], feasibility studies are not adequately powered to test the hypothesis of the efficacy of physical activity intervention, and therefore, a priori criteria for progression to the definitive large-scale RCT is advisable to consider future efforts. The progression criteria to a definitive large-scale RCT were (1) no any serious adverse events, such as hospitalisation, life-threatening condition, death and any adverse events associated with the intervention experienced by less than 5% of participants per group; (2) recruitment rate of no less than 75% by the end of the 4-month recruitment period; and (3) retention rate of no less than 75% in each group at 12 weeks (end-point). If all the three criteria were not met, there would be insufficient evidence to justify proceeding to the definitive RCT. Changes will be required to be made to the intervention with the consequent re-running of the intervention a few months later.

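### Progression criterion 1 does not deliver its stated tolerance: at 20 per group, below 5% means no affected participant, and the serious-event clause as worded is not limited to related events

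*Protocol article*

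**What the plan says.** The Progression criteria section of the protocol article lists three conditions for moving to the definitive trial. The first has two parts in one sentence: "no any serious adverse events, such as hospitalisation, life-threatening condition, death", and then "any adverse events associated with the intervention experienced by less than 5% of participants per group". The section goes on: "If all the three criteria were not met, there would be insufficient evidence to justify proceeding to the definitive RCT". It then calls for the intervention to be changed and run again a few months later.

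The Sample size section states that "a total target sample of 40 older adult participants will be recruited", "with 20 in the intervention group and 20 in the wait-list control group". The section on recruitment and retention rates treats that total as a floor ("to a minimum of 40 participants"), at 10 a month over 4 months.

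The inclusion criteria admit people aged 60 or over, healthy or with one or more common chronic diseases, who must be ambulatory and score at least 9 of 12 on the physical performance battery. The WLC group section says that the wait-list arm starts the intervention only after its follow-up measures, about 12 weeks after randomisation.

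**The concern.** A percentage threshold implies that some affected participants are acceptable. Here the percentage and the group size do not fit: the smallest non-zero proportion that a group of 20 can show already breaches the limit. The clause has no severity limit, so one minor walking-related complaint would fail it.

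The serious-event part is an absolute zero. In the sentence as written, the words on association with the intervention attach to the second part, not to the serious events. A hospital admission with no connection to the walks would therefore count, in either arm.

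The rule is one of three that decide whether a definitive trial goes ahead. If it is applied as written, one minor related event or one unrelated admission can block progression. If it is not, the team will have to decide what it meant after seeing the events.

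**Working it through.** **Inputs from the article.** 20 per group and 40 in total (Sample size); a limit strictly below 5% per group and no serious events (Progression criteria); 12 weeks to the end-point. The total agrees with the article's own arithmetic: 20 + 20 = 40, and 10 a month × 4 months = 40. There is no power or precision calculation to reproduce.

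**Step 1. What the limit permits.** Find the largest whole number k with k/n < 0.05.

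| n per group | 1/n | Permitted k |
|---|---|---|
| 15 (75% of 40 = 30, split equally) | 6.7% | 0 |
| 19 | 5.3% | 0 |
| 20 | 5.0% | 0 |
| 21 | 4.8% | 1 |

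A limit of at most 5%, instead of below 5%, would permit 1 at n = 20.

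**Step 2. Chance of failing the related-event clause in one group of 20.** With true rate p, failure under the clause as written is P(at least 1) = 1 − (1 − p)^20. If one affected participant were tolerated, failure would be P(at least 2) = 1 − (1 − p)^20 − 20p(1 − p)^19.

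| True rate p | Fails as written | Fails if one is tolerated |
|---|---|---|
| 1% | 18% | 2% |
| 2% | 33% | 6% |
| 3% | 46% | 12% |
| 4% | 56% | 19% |

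All four rates are inside the article's own limit. At 4%, a group of 20 fails more often than it passes.

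**Step 3. Chance of failing the serious-event clause through background illness.** The article gives no background risk, so the 12-week risk q is an assumption, shown as a range. Failure is 1 − (1 − q)^n.

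| Assumed 12-week risk q | n = 40 (both arms) | n = 20 (one arm) |
|---|---|---|
| 0.5% | 18% | 10% |
| 1% | 33% | 18% |
| 2% | 55% | 33% |
| 3% | 70% | 46% |
| 5% | 87% | 64% |

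The chance reaches 50% at q = 1 − 0.5^(1/40) = 1.7% for 40 people, or 1 − 0.5^(1/20) = 3.4% for 20.

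**Step 4. The wait-list arm.** Criterion 1 applies an intervention-associated rate per group and gives no time window. Criterion 3 does give one: "retention rate of no less than 75% in each group at 12 weeks (end-point". Up to 12 weeks the wait-list arm has received nothing with which an event could be associated; after that it receives the intervention. The criterion does not say which period is meant.

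**The case against.** **The rule can be applied.** A reader might infer that the criterion is unworkable at this size. It is not: it operates as zero tolerance, and since 40 is a minimum, a group of 21 would be allowed one event. This stands, and it limits the point to a mismatch between the stated percentage and the planned size.

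**A harmless intervention passes the related-event clause.** An intervention that causes no events fails that clause only through misattribution. The failure rates in Step 2 concern interventions with a low but real event rate that the article itself calls acceptable. This stands too. For a truly harmless intervention, the route to failure is mainly the serious-event clause.

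**That clause can be read more generously, and its risks are assumed.** The sentence is loose, and the qualifier could be stretched over both parts. The literal reading is the narrower one, and the need to choose between readings is itself the defect. The background risks are not in the article, and the mobility and cognition requirements select fitter people. Hence the wide range.

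**The wait-list arm does have exposure later.** Because it is a delayed-intervention arm and criterion 1 has no time limit, a per-group rate can have meaning for both arms. Dropping that arm from the criterion is therefore not clearly right; the period needs stating.

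**Event collection.** The Data monitoring section says "The PhD student is responsible for monitoring and reporting spontaneous adverse events", and a reader might infer that events are gathered by spontaneous report alone. The same sentence also covers unintended trial effects, and an article commonly leaves ascertainment procedures to the full protocol. Nothing is claimed here on that.

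**What a pass shows.** Observing 0 of 20 has a one-sided 95% upper limit of 1 − 0.05^(1/20) = 13.9%. The article does not claim that passing proves a rate below 5%, so this contradicts nothing in it.

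**The consequence may be softer.** Failure leads to changes and a re-run. The wording about all three criteria not being met could mean that any one fails or that all fail; on the second reading a safety failure alone would not block progression. That makes the decision rule less clear and does not repair the threshold.

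**Conclusion.** The point holds as a badly fixed decision threshold. At the planned 20 per group, and at any smaller size, the 5% tolerance is a tolerance of zero. This follows from the article's own figures and needs no assumption. Related-event rates of 2% and 4%, inside the stated limit, would fail in about 33% and 56% of groups of 20, assuming independent participants.

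On its literal wording, the serious-event clause also has no relatedness limit. The resulting chance of failing on unrelated illness, about 18% to 87% among 40 people, rests on an assumed 12-week risk of 0.5% to 5% and on counting both arms. It shows that the problem could be material; it does not estimate how likely failure is in this trial.

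**What to change.** 1. State the related-event limit as a whole-participant count at the achieved group size. As written it is 0 of 20; if one affected participant is meant to be tolerable, it should read no more than 1 of 20, with the count for other group sizes given. The team sets the count.
2. State explicitly whether the serious-event clause is limited to events judged related to the intervention. If it is, list unrelated serious events descriptively by arm. If an all-cause trigger is intended, say so.
3. State the period in which an event can count as associated with the intervention in each arm, given that the wait-list arm receives nothing before its 12-week follow-up.
4. Report the observed proportion in each arm with an exact confidence interval.

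The cost is mainly wording, with two real downsides. If relatedness is required, the decision depends on a judgement, and the Data monitoring and Randomisation and concealment sections show that the researcher who monitors and reports events also conducts the walks and is not blinded. The Trial status section says that recruitment began in October 2017, so this would alter a pre-specified criterion in a running trial. The change should be dated, justified and made before outcome data are reviewed.

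### The no-go sentence for the definitive trial can be read as requiring all three criteria to fail or only one, and it does not match the re-run rule in the section before it

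*Protocol article*

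**What the plan says.** The Progression criteria section sets three conditions for moving to the definitive trial. The first is safety: no serious adverse events, and "any adverse events associated with the intervention experienced by less than 5% of participants per group". The second is "recruitment rate of no less than 75% by the end of the 4-month recruitment period". The third is added with a conjunction: "and (3) retention rate of no less than 75% in each group at 12 weeks (end-point". The consequence follows: "If all the three criteria were not met, there would be insufficient evidence to justify proceeding to the definitive RCT". The next sentence has no condition of its own, so it appears to hang on the same one: "Changes will be required to be made to the intervention with the consequent re-running of the intervention a few months later".

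The section just before it, Recruitment and retention rates, uses the same 75% figures with an either/or trigger. It acts if the number recruited is below 75% "by the end of the 4-month recruitment period or if the retention rate is less than 75% at 12 weeks". Its consequence is that "changes will be made to the recruitment strategy and the intervention will run again a few months later". The same section says that no targets were set for the other feasibility outcomes, such as questionnaire completion or session attendance.

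**The concern.** The three criteria are the only pre-specified thresholds for deciding whether a definitive trial is justified, and informing that trial is the purpose of the study. The sentence that turns them into a decision has two readings:

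- *All three fail*: the no-go applies only when safety, recruitment and retention are all missed.
- *Not all are met*: the no-go applies when any one of them is missed.

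No other part of the article says what one or two failures mean for progression. Two people holding the same results could therefore reach opposite conclusions, and the more lenient reading is the literal one. The preceding section adds to the difficulty. It shares two thresholds and the re-run with the progression rule, but it triggers on either shortfall, states retention differently and names a different thing to change.

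**Working it through.** **Inputs.** Ten participants a month over a 4-month recruitment period (Recruitment and retention rates); 20 per group (Sample size); 75% thresholds for recruitment and retention (both sections); retention applied to each group (Progression criteria only).

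**The plan's own figure.** 10 × 4 = 40 = 20 + 20, so the target is reproduced. If the recruitment threshold is a share of that target, it is 0.75 × 40 = 30 recruits. Per-group retention is 0.75 × 20 = 15 of 20.

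**Step 1: all pass/fail patterns.** Each criterion passes or fails, giving 2 × 2 × 2 = 8 patterns. Retention is treated here as one pass/fail result; step 2 takes up how it is defined.

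| Safety | Recruitment | Retention | No-go if *all three fail* | No-go if *not all are met* | Re-run under Recruitment and retention rates |
|---|---|---|---|---|---|
| pass | pass | pass | no | no | no |
| pass | pass | fail | no | yes | yes |
| pass | fail | pass | no | yes | yes |
| pass | fail | fail | no | yes | yes |
| fail | pass | pass | no | yes | no |
| fail | pass | fail | no | yes | yes |
| fail | fail | pass | no | yes | yes |
| fail | fail | fail | yes | yes | yes |
| **Total** | | | **1 of 8** | **7 of 8** | **6 of 8** |

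Six patterns have one or two failures. In five of them the re-run is ordered while the literal no-go does not apply. In the sixth, safety failing alone, neither rule acts under the literal reading. Under the other reading, all six re-run patterns fall among the seven that block progression, so the either/or conflict disappears.

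**Step 2: the retention threshold.** Suppose 14 of 20 are retained in one group and 17 of 20 in the other.

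- Overall: (14 + 17) / 40 = 31/40 = 77.5%. This is at least 75%, so the re-run rule read overall is not triggered.
- Per group: 14/20 = 70%, below 75%, so the progression criterion fails.

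The mismatch runs one way. If both groups keep at least 15 of 20, the total is at least 30 of 40, so a per-group pass always implies an overall pass. The unqualified version is the laxer one.

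**Step 3: what is changed.** Recruitment and retention rates prescribes a change to the recruitment strategy even when retention is what fell short. Progression criteria prescribes a change to the intervention even if recruitment is what fell short. Both are followed by a re-run a few months later.

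**Step 4: the recruitment denominator.** The wording in Recruitment and retention rates, a number of recruited participants set against a minimum of 40, points to a share of the target. Progression criteria instead speaks of a recruitment rate, which Feasibility outcomes defines as responders divided by invitations and advertisements, with 25% (48/195) as its example. The 30-of-40 threshold is therefore an inference that the article should state.

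**The case against.** The strongest defence is that the intent is clear. The criteria are listed conjunctively, so a study that misses one has not met the stated criteria, and in ordinary English the sentence can mean that not all were met. On that reading there is no clash with the either/or trigger. The sentence is also a one-way conditional: it says when evidence is insufficient and does not say that progression is justified otherwise. All of this stands. A reader might infer that the plan permits the main trial unless all three criteria fail; the documents do not establish that.

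Two further inferences would go too far. One is that the two sections disagree for every study with one or two failures. They do not, because a safety failure alone triggers neither. The other is that a study with a serious adverse event and poor retention would meet no obstacle so long as recruitment passed. If overall retention were below 75%, the preceding section would already order changes and a re-run.

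It is also fair to say that the two sections govern different decisions, one re-running the feasibility study and the other progressing from it. They nevertheless share thresholds and the re-run. The differences on retention and on what is changed remain under either reading of the no-go sentence.

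**Conclusion.** The point holds as a wording defect in the study's only pre-specified go/no-go rule, together with a mismatch between two adjoining sections. It does not show that a lenient rule was intended; the list points the other way. The two readings block 1 and 7 of the 8 patterns. Under the literal one, the sections diverge in 5 of the 6 patterns with one or two failures, and a safety failure alone is caught by neither.

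These counts need no assumption beyond treating each criterion as pass or fail. They are counts of patterns, not probabilities: the article gives no expected failure rates, so a claim about how often the readings would lead to different decisions has no support in it. The retention example assumes full groups of 20 and that the unqualified threshold is read over both groups together.

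**What to change.** In Progression criteria, replace the condition with one that has a single meaning, for example: *If any one of the three criteria is not met, proceeding to the definitive RCT is not justified without changes and re-assessment.* This also covers a safety failure on its own.

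Then reconcile Recruitment and retention rates with it:

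- Use the same per-group retention threshold in both sections.
- State in both that the 75% for recruitment is a share of the target of 40.
- Link what is changed to the criterion that failed, in place of the recruitment strategy in one section and the intervention in the other.

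The section already joins its two shortfalls with an either/or, so that part can stay.

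The cost is a few words and a rule stricter than its literal wording. Trial status gives October 2017 as the start of recruitment, so some recruitment data may already be known. The change should be dated and should say which results had been seen when it was made.
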